## **5.3 Study visit schedule**

### **5.3.1 Visit 1**

- Review of signed Consent form
- Review of eligibility criteria
- Documentation of previous medical history
- Documentation of previous influenza illness
- Documentation of previous influenza vaccination
  
- Baseline blood sample taken (10 mls)
  - FBC + differential
  - Lymphocyte subset
  - IgG, IgA, IgM
  - Cellular response to influenza vaccine
  - HI antibody titer
  
- 1st dose of influenza vaccine given
  - Pre-vaccination medical check
  - Post-vaccination 30 minute observation
  - Acute AE(s) documented and reported (see Section 8.0 for details)
  
- 7-day post-vaccine check phone call for documentation and reporting of AEFI(s) (see Section 8.0 for details)
  
- Optional blood sample taken 2 weeks after vaccination (5 mL)
  - Cellular response to influenza vaccine
  - HI antibody titer

### **5.3.2 Visit 2**

- Review of ongoing eligibility
- Documentation of influenza-like illness
- Delayed AE(s) documented and reported (see Section 8.0 for details)
  
- Blood sample taken (7 mls)
  - FBC + differential
  - Cellular response to influenza vaccine
  - HI antibody titer
  
- 2nd dose of Influenza vaccine given
  - Pre-vaccination medical check
  - Post-vaccination 30 minute observation
  - Acute AE(s) documented and reported (see Section 8.0 for details)

- 7-day post-vaccine check phone call for documentation and reporting of AEFI(s) (see Section 8.0 for details)
- Optional blood sample taken 2 weeks after vaccination (5 mL)
  - Cellular response to influenza vaccine
  - HI antibody titer

### 5.3.3 Visit 3

This is the exit evaluation visit for participants  $\geq 9$  years of age. For these participants the following will be performed:

- Documentation of influenza-like illness
- Delayed AE(s) documented and reported (see Section 8.0 for details)
- Blood sample taken (5 mls)
  - Cellular response to influenza vaccine
  - HI antibody titer

For participants  $< 9$  years\* of age, the following will be performed:

- Review of ongoing eligibility
- Documentation of influenza-like illness
- Delayed AE(s) documented and reported (see Section 8.0 for details)
- Blood sample taken (7 mls)
  - FBC + differential
  - Cellular response to influenza vaccine
  - HI antibody titer
- 3rd dose of Influenza vaccine given
  - Pre-vaccination medical check
  - Post-vaccination 30 minute observation
  - Acute AE(s) documented and reported (see Section 8.0 for details)
- 7-day post-vaccine check phone call for documentation and reporting of AEFI(s) (see Section 8.0 for details)
- Optional blood sample taken 2 weeks after vaccination (5 mL)
  - Cellular response to influenza vaccine
  - HI antibody titer

\*children aged 6 to 35 months will only receive the 3rd influenza vaccine dose if an initial safety run in phase determines that the third dose of the vaccine is safe and tolerable in children aged 3 -  $< 9$  years of age (see Section 8.3.4)

### 5.3.4 Visit 4

This is the exit evaluation visit for participants <9 years of age.  
For these participants the following will be performed:

- Documentation of influenza-like illness
- Delayed AE(s) documented and reported (see Section 8.0 for details)
- Blood sample taken (5 mls)
  - Cellular response to influenza vaccine
  - HI antibody titer

Participants will have the option for additional blood samples to be taken in between the scheduled study visits to evaluate the kinetics of the immune response. In this instance 5 mls of blood will be taken to measure cellular response and HI antibody titers. This will be optional and only performed if the participant's CVAD is being accessed for treatment or routine investigational purposes at the time.

## **6.0 VACCINE**

### **6.1 Influenza vaccine**

The influenza vaccine used during the study period will be subject to seasonal recommendations set by the ATAGI, the Australian Influenza Vaccine Committee (AIVC), and the World Health Organization (WHO). All vaccines must be registered by the Therapeutic Goods Administration (TGA) to meet eligibility criteria set by the Australian Department of Health.

Currently, the following vaccines are recommended:

#### **FluQuadri Junior**

For children aged  $\geq 6$  months to <3 years  
Administration route: intramuscular injection  
Sponsor: Sanofi-Aventis Australia  
Quadrivalent inactivated influenza vaccine  
Each 0.25 mL pre-filled syringe contains:  
7.5  $\mu$ g hemagglutinin for each of the 4 recommended influenza virus strains  
 $\leq 50$   $\mu$ g formaldehyde  
 $\leq 125$   $\mu$ g octoxinol 9  
 $\leq 0.5$   $\mu$ g ovalbumin

#### **FluQuadri**

For children aged  $\geq 3$  years  
Administration route: intramuscular injection  
Sponsor: Sanofi-Aventis Australia  
Quadrivalent inactivated influenza vaccine  
Each 0.5 mL pre-filled syringe contains:  
15  $\mu$ g hemagglutinin for each of the 4 recommended influenza virus strains  
 $\leq 100$   $\mu$ g formaldehyde

≤250 µg octoxinol 9

≤1 µg ovalbumin

Annual influenza vaccination is recommended before the influenza season starts. Influenza community circulation usually peaks between June and September in most parts of Australia. The influenza vaccine usually becomes available in March or April of each year.

If more than one influenza vaccine is recommended, these should be administered 4 weeks apart. The first vaccine should be administered as soon as it becomes available to ensure that there is enough time to receive the second (and third dose) before influenza circulation peaks.

## **6.2 Contraindications and precautions**

The only absolute contraindication to influenza vaccine is anaphylaxis after a previous dose of any influenza vaccine or any of the components of the influenza vaccine.

Children or adolescents with a known egg allergy, including history of anaphylaxis to egg, can be safely vaccinated with influenza vaccines (36). Those with a history of anaphylaxis must receive their influenza vaccine in a medical facility with staff experienced in recognising and treating anaphylaxis, such as Perth Children's Hospital. These children need a minimum 30 minute check post vaccination.

Some studies suggest that patients receiving immunological treatment for cancer, such as the checkpoint inhibitors (PD-1 inhibitor, Nivolumab; PD-L1 inhibitor, Pembrolizumab; CTLA-4 inhibitor, Ipilimumab) may have a higher risk of immune-mediated adverse events following the influenza vaccination (37). A more recent study on patients receiving a single checkpoint inhibitor has not confirmed these findings (38). Currently, the decision on proceeding with influenza vaccination in patients receiving immune checkpoint inhibitors is at the discretion of the treating Oncologist.

All influenza vaccines available in Australia are inactivated vaccines, so they cannot cause influenza. Nonetheless, post-vaccination symptoms can mimic influenza infection. 1-10% of people who receive a standard inactivated influenza vaccine develop fever, malaise and/or myalgia. These adverse events can start a few hours after vaccination and may last for 1-2 days.

## **7.0 LABORATORY EVALUATIONS**

### **7.1 Assessment of humoral response to influenza vaccine**

Blood samples obtained for the purpose of the humoral response to the influenza vaccine assessment will be centrifuged and sera stored at -80°C. At the end of the influenza season, predicted to be in October, the samples will be sent to the Victorian Infectious Diseases Reference Laboratory (VIDRL) at the Peter Doherty

Institute for Infection and Immunity in Melbourne, Victoria. This centre is a WHO Collaborating Centre for Reference and Research on Influenza and is part of the WHO Global Influenza Surveillance Network organisation (WHO GISN).

HI antibody titers against each vaccine strain will be measured in each sample by standardised assay developed and updated by the WHO GISN (39).

## **7.2 Assessment of cellular response to influenza vaccine**

The cellular response to the influenza vaccine will be assessed in [name] laboratory at the Telethon Kids Institute (TKI). Levels of IFN- $\gamma$  produced by T lymphocytes stimulated by influenza vaccine concentrate *in vitro* will be measured using sandwich immune-enzyme technology (ELISpot).

## **7.3 Laboratory testing for influenza infection**

Nasopharyngeal swabs obtained from patients with ILI will undergo direct immunofluorescence testing for a range of respiratory viruses including influenza A and B. If negative, real-time PCR assay will be performed targeting matrix genes of Influenza A and B.

Nasopharyngeal swabs positive for Influenza A or B will be sent to VIDRL for influenza strain typing.

## **8.0 SAFETY, ADVERSE EVENT MONITORING AND REPORTING**

### **8.1 Adverse events following immunisation (AEFIs)**

#### **8.1.1 Definition and Grading of AEFIs**

Adverse events following immunisation are defined as unwanted or unexpected events following the administration of a vaccine. AEFIs also include conditions that may occur following the incorrect handling and/or administration of a vaccine.

The intensity of AEFIs will be graded on a three-point scale – mild, moderate, severe. For purposes of consistency, the intensity grades are defined as:

- Mild                Does not interfere with subject's usual function.
- Moderate        Interferes to some extent with subject's usual function.
- Severe            Interferes significantly with subject's usual function.

#### **8.1.2 Relationship of AEFIs to the influenza vaccine**

To ensure consistency of AEFIs causality assessment, investigators will apply the following general guideline:

- **Related event:** There is a plausible temporal relationship between the onset of the AE and administration of the influenza vaccine, and the AE cannot be readily explained by the subject's clinical state, intercurrent illness, or concomitant therapies.
- **Unrelated event:** Evidence exists that the AE has aetiology other than the influenza vaccine and/or the AE has no plausible temporal relationship to the influenza vaccine administration.
- **Expected event:** An AE that is commonly reported by drug trial participants and listed in the product information brochure.
- **Unexpected event:** An unexpected event is an AE not listed in the product information brochure. This includes AEs for which the specificity of severity is not consistent with the description in the product information brochure.

### 8.1.3 Definition of a mild and moderate AEFI

A mild and moderate AEFI is an adverse event following the influenza vaccine that is expected and of a mild to moderate grade. The most commonly reported mild and moderate AEFIs are listed below:

#### 1. Local:

- **Tenderness**
  - Mild - hurts if gently touched (subject whimpers, winces, protests or withdraws)
  - Moderate - hurts if gently touched with crying
- **Erythema**
  - Mild - 0.5 to 2.0 cm
  - Moderate - >2.0 cm to 7.0 cm
- **Swelling/induration**
  - Mild - ≤1.0 cm
  - Moderate - 1.0 to 5.0 cm

#### 2. Systemic:

- **Fever**
  - Mild - 38.0 to 39.0 °C
  - Moderate - >39.0 - 40.0 °C
- **Irritability**
  - Mild - easily consolable
  - Moderate - requiring increased attention
- **Drowsiness**
  - Mild - increased or prolonged sleeping bouts
  - Moderate - slightly subdued interfering with daily activity

- Decreased appetite
  - Mild - decreased interest in eating
  - Moderate - decreased oral intake
- Vomiting
  - Mild - easily tolerated by the participant, causing minimal discomfort and does not interfere with everyday activities
  - Moderate - sufficiently discomforting to interfere with normal everyday activities
- Diarrhoea
  - Mild - easily tolerated by the participant, causing minimal discomfort and does not interfere with everyday activities
  - Moderate - sufficiently discomforting to interfere with normal everyday activities
- Myalgia
  - Mild muscle pain
  - Moderate muscle pain, limiting instrumental ADL but not self-care
- Headache
  - Mild headache
  - Moderate headache, limiting instrumental ADL but not self-care

#### 8.1.4 Definition of a serious AEFI

A serious AEFI is an AE at least possibly related to the study vaccine that is:

- life-threatening
- requires inpatient hospitalization or prolongation of existing hospitalization\*
- results in persistent or significant disability/incapacity
- results in death

\* Serious AEFI in the case of hospitalization or prolongation of existing hospitalization for fever is defined as hospitalization or prolongation of existing hospitalization with fever >40.5 °C

Examples of serious AEFIs are:

1. **Anaphylaxis** - anaphylaxis following immunization has been reported, but generally occurs very rarely. In the case of influenza vaccine, these probably represent an allergic response to a residual component of the manufacturing process, most likely egg protein. Anaphylaxis to egg is not a contraindication to administration of the influenza vaccine. The only absolute contraindication to influenza vaccine is anaphylaxis after a previous dose of any influenza vaccine or any of the components of the influenza vaccine.
2. **Hypotonic-hyporesponsive episode (HHE)** - HHE is a sudden onset of pallor and cyanosis, muscle hypotonia and reduced responsiveness or unresponsiveness occurring after vaccination, where no other cause is evident such as a vasovagal episode or anaphylaxis. The episode usually

occurs 1 - 48 hours after vaccination and resolves spontaneously. There are no known long-term side effects of HHE.

3. **Febrile convulsion** - febrile convulsions are rare following immunisation. They do occur more commonly, but still at a low rate, after some vaccines. For example, MMR and MMRV vaccines are associated with an increased risk of febrile convulsions approximately 7 to 12 days after the 1st vaccine dose (40, 41).

In 2010, higher rates of fever and febrile convulsions occurred in children aged <5 years after influenza vaccination, especially in children aged <3 years. These were specifically associated with the vaccines Fluvax and Fluvax Junior at a rate of 4.4 per 1000 doses, compared with no such events reported among children who received an alternative vaccine in the same year (42). As a consequence, Fluvax and Fluvax Junior vaccines are no longer available in Australia.

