## **5.0 STUDY DESIGN**

### **5.1 Type of study**

This will be a prospective non-randomised, open label study.

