### **5.2 Study interventions**

Each visit will comprise of two main components:

1. A blood sample will be taken to perform the following tests:
  - a. A full blood count (FBC) including the differential will be requested prior each vaccination. Vaccination will only proceed if absolute neutrophil count (ANC) is  $\geq 0.5 \times 10^9/L$ , as per the Australian Immunisation Handbook 10th Edition recommendations.
  - b. Lymphocyte subsets (prior Visit 1 only). This is to measure the number of B-cells, CD4 and CD8 positive T-cells, NK cells and memory T and B-cells.
  - c. IgG, IgA and IgM levels (prior Visit 1 only).
  - d. Cellular response to the influenza vaccine.

- e. HI antibody titer measurement.
- 2. Influenza vaccine will be given (with the exception of the exit visit) to the participant after a baseline medical check. Participants found to be physically unfit will have their vaccination postponed. A minimum 30 minute observation period will be provided to monitor for development of an acute adverse event (AE) to the vaccine.

Participant age, sex, primary oncological diagnosis and phase of treatment will be documented at the start of the study. A detailed medical history will be taken including history of previous influenza illness, influenza immunisation and allergy to egg.

A substantial effort will be made to schedule study visits to coincide with participants' regular follow up outpatient visits and appointments for chemotherapy. Where possible, blood samples will be obtained from accessed central venous access devices (CVAD) to spare participants from venepunctures solely for study purposes.

Study visits will be spaced by a minimum of 4 weeks and maximum of 6 weeks as per the Australian Immunisation Handbook 10th Edition recommendations regarding timing of influenza vaccination and to allow for flexibility in arranging suitable appointments for study participants.

Any AEs post influenza vaccination will be documented at each visit. Each participant's parent/guardian will also be contacted by telephone one week after the influenza vaccination to document any delayed AEs related to the influenza vaccine.

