## 8.3 Reporting and monitoring of AEFIs

### 8.3.1 Reporting responsibilities

Immunisation providers and medical practitioners in WA have a statutory requirement to notify AEFIs to the WA Department of Health through the WA Vaccine Safety Surveillance (WAVSS) System. The WAVSS reporting system is part of national reporting associated with the national network on Adverse Events Following Immunisation - Clinical Assessment Network (AEFI-CAN) (43).

Participants who receive their vaccine at the Stan Perron Immunisation Centre at PCH will be involved in automated surveillance with AusVaxSafety, a national vaccine safety initiative led by the National Centre of Immunisation Research and Surveillance (NCIRS) and funded by the Australian Department of Health.

Mild and moderate AEFIs do not require reporting to the WAVSS. These will be recorded, as well as any other AEFIs, by the study investigators as part of the Safety objectives evaluation.

A comprehensive list of AEFIs requiring reporting via the WAVSS System can be found in Appendix I. It includes the following entities:

- Abscess
- Acute flaccid paralysis
- Allergic reaction (generalised)
- Anaphylaxis
- Arthralgia
- Arthritis
- Brachial neuritis
- Death
- Encephalopathy
- Encephalitis
- Extensive limb swelling
- Fever >40.5 °C
- Guillain-Barré syndrome
- Hypotonic-hyporesponsive episode
- Injection site reaction (severe), including nodule
- Intussusception
- Lymphadenitis
- Meningitis
- Orchitis
- Osteitis
- Osteomyelitis
- Parotitis
- Severe and/or unusual rash
- Screaming
- Thrombocytopenia <50 x 10^9/L
- Toxic shock syndrome
- Vasovagal episode

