### **8.3.2 Required reporting criteria**

The following information regarding AEFI(s) will be recorded by the study investigators:

- Event description
- Event grade
- Event duration
- Relationship to the influenza vaccine (related or unrelated event)
- Event expectedness (expected or unexpected event)
- Action taken by the Study investigator
- Required medical attention

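### Section 8.1.4 makes vaccine-relatedness part of what counts as serious, so the serious AEFI count is not all-cause and can hide an excess after the extra dose

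*Protocol*

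**What the plan says.** Section 8.1.1 sets no causality condition for an AEFI: "Adverse events following immunisation are defined as unwanted or unexpected events following the administration of a vaccine". Section 8.3.1 says of mild and moderate AEFIs: "These will be recorded, as well as any other AEFIs, by the study investigators as part of the Safety objectives evaluation". Section 8.3.2 lists the fields to be recorded: description, grade, duration, relatedness (two levels), expectedness, action taken and medical attention needed.

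Section 8.1.4 then defines seriousness differently: "A serious AEFI is an AE at least possibly related to the study vaccine that is", followed by life-threatening, hospitalisation, disability and death. A footnote narrows hospitalisation for fever to temperatures above 40.5 °C.

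On causality, section 8.1.2 says "To ensure consistency of AEFIs causality assessment, investigators will apply the following general guideline". A related event needs a plausible temporal relationship and, in addition, that "the AE cannot be readily explained by the subject's clinical state, intercurrent illness, or concomitant therapies". An unrelated event needs evidence of another cause, or no plausible temporal link, or both. On blinding, section 5.1 says: "This will be a prospective non-randomised, open label study".

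The serious category is used in the 24-hour report (8.3.3) and the stopping rule (8.4). The DSMB also receives a safety report on six children aged 3 to under 9 years before the three-dose schedule opens to those aged 6 to 35 months (8.3.4).

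**The concern.** Seriousness describes what happened to the child; relatedness is an opinion about why. Section 8.1.4 merges them, so the opinion decides whether the outcome is counted. Causality is then applied twice, first as a condition of entry to the serious category and again as a recorded field.

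This matters more here than in most vaccine studies. Participants are receiving cancer therapy or are within six months of completing it (section 4.1), so a competing explanation for a death or an admission will often be available. The person judging knows which dose has just been given. With no concurrent control, the main internal check on the extra dose is a count of serious events in each dose interval, whatever their presumed cause. A count already filtered on attribution cannot serve that purpose. An excess made up of events that look like complications of chemotherapy would be removed before anyone tabulated it.

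**Working it through.** The protocol states no safety rate or threshold on this point, so there is no figure to reproduce. The check is mainly a comparison of the text.

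**Step 1: which events leave the serious count.** Take an admission two weeks after the extra dose that the investigator attributes to chemotherapy, with evidence.
- Under 8.1.1 it is an AEFI, because it follows vaccination and is unwanted.
- Under 8.1.2 it is unrelated.
- Under 8.1.4 it is not serious, although it meets the hospitalisation criterion.
- Under 8.3.2 it is recorded as unrelated, with nothing to mark that it met a seriousness criterion.

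**Step 2: the two causality scales do not match.** Section 8.1.4 speaks of a possible relation; 8.1.2 and 8.3.2 offer only related and unrelated. An event with a ready alternative explanation, but no evidence for it, meets neither definition in 8.1.2. One investigator could treat it as possibly related and hence serious, and another could not. How much the filter removes therefore depends on a reading the protocol leaves open.

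**Step 3: whether intensity grade can stand in.** Section 8.1.1 grades by interference with usual function, not by outcome. Sections 5.2 and 8.1.3 show the gap: a child with a single temperature of 38.5 °C goes to the Emergency Department and is admitted, yet 38.0 to 39.0 °C is graded mild. (That admission is also outside the serious category through the fever footnote. It is used here only to show that grade does not track hospitalisation.) All-cause serious events would have to be inferred from the description and the medical-attention field.

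**Step 4: other filters.** The one-week telephone call is "to document any delayed AEs related to the influenza vaccine", which is narrower than 8.1.1, although section 5.2 also has any AEs documented at each visit. In Appendix I, the entry for death applies only where no other clear cause can be established.

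**Step 5: illustration only.** Two inputs are assumptions that the documents do not supply: the all-cause probability *q* that a child has a serious event in one dose interval (5% to 30%), and the share *a* attributed elsewhere (0% to 95%). The 80 children come from section 3.7. That all 80 receive the extra dose is a further assumption, since for ages 6 to 35 months it depends on the run-in.

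Expected counted events = 80 × *q* × (1 − *a*):

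| *q* | *a* = 0 | 50% | 80% | 95% |
|---|---|---|---|---|
| 5% | 4.0 | 2.0 | 0.8 | 0.2 |
| 10% | 8.0 | 4.0 | 1.6 | 0.4 |
| 30% | 24.0 | 12.0 | 4.8 | 1.2 |

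For the six run-in children, the chance that at least two are counted is 1 − (1 − p)^6 − 6p(1 − p)^5, with p = *q*(1 − *a*). At *q* = 10% this is 11.4% unfiltered, 3.3% with half removed and 0.6% with 80% removed. At *q* = 30% it is 58.0%, 22.4% and 4.6%. Two is only a yardstick; the protocol sets no threshold for the run-in report.

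**Step 6: what all-cause counting could show.** Suppose the rate doubles from 10% to 20% after the extra dose, with intervals independent within a child. Then d = 0.10 and the discordant proportion is π = 0.10 × 0.80 + 0.20 × 0.90 = 0.26. Two-sided McNemar power is Φ[(d√80 − 1.96√π)/√(π − d²)] = Φ[(0.894 − 0.999)/0.5] = Φ(−0.21), about 42%. If the filter removes 50% or 80% of events in both intervals, power is about 22% or 11%. The same formula reproduces the 80% and 90% powers in section 9.2 (79.8%, 80.3%, 90.1% and 90.0%).

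**The case against.** The strongest reply is that nothing is lost. AEFIs are defined without causality and all are recorded. Severe AEFIs go to the DSMB within 48 hours with no relatedness condition, unexpected ones are also sent, and the periodic reports are issued whatever the degree of the events (8.3.3, 8.3.4). A death or life-threatening event would reasonably be graded severe. This stands. A reader might infer that the safety objective cannot show an excess, that the DSMB cannot revisit causality, or that the serious count will sit at zero. The protocol supports none of these.

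Second, section 2.1 states a descriptive objective with no comparison between doses. The extra dose always comes last, so dose interval is confounded with time and treatment phase, and power is poor even unfiltered. This also stands, and it limits what the repair can achieve. It does not justify adding a bias to the count.

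Third, deleting the relatedness condition would not give a count of all admissions, because the fever footnote still excludes fever admissions at or below 40.5 °C. Correct. The table in Step 5 should not be read as a forecast of admissions.

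Fourth, data fields and tables can be left to the case report form or the SAP. That is true of a missing table. Here the protocol itself fixes the definition, and any form or table using the term serious AEFI would inherit it.

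**Conclusion.** The point holds as a fault in a stated definition. Followed as written, section 8.1.4 gives a serious count that depends on open-label attribution and is not all-cause. The direction is downward, and an excess after the extra dose could be partly or wholly masked in that count. The run-in report is also affected to the extent that it relies on the serious category.

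The size cannot be stated from the documents, which give neither an admission rate nor the share of events attributed to cancer treatment. The figures above show only how the loss scales under assumed values. The underlying events remain in the AEFI record, so the loss is in classification and in what can be read directly, not in collection as a whole. Even with the definition repaired, 80 children and no concurrent control leave limited ability to show an excess.

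**What to change.** - **8.1.4:** define a serious AEFI by the outcome criteria alone, dropping the qualifier about possible relation to the vaccine. State explicitly that the footnote limits which fever admissions are counted.
- **8.3.2:** add a field for the seriousness criterion met, beside the existing relatedness field.
- **DSMB reports, including the run-in report, and final analysis:** list every serious AEFI with its relatedness, and tabulate by dose number (standard versus extra), all-cause and related.
- **8.3.3 and 8.4:** write the relatedness condition into these sections explicitly, so that the 24-hour report and the stopping triggers keep their present scope. No change to those rules is proposed.
- **Causality scale:** reconcile the possible-relation wording of 8.1.4 with the two-level scale in 8.1.2 and 8.3.2, and say where an event with a ready but unproven alternative explanation falls.
- **5.2:** align the description of the one-week call with 8.1.1 and 8.3.1.

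The cost is protocol wording and one form field. Expedited reporting does not grow. The downside is a longer serious-event listing that includes treatment-related admissions, with the relatedness column there to help readers interpret it.
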